---

## 0. schema

[figure not shown]

\*If there are MRI images that meet the criteria within 3 months prior to registration, they should be used.

### 0.1. summary of clinical research design

Study Design: A prospective, interventional, Phase II, multicenter, open-label study with a pre- and post-treatment comparative design

### 0.2. type of clinical research

Type of clinical research: Specific clinical research (with unapproved or off-label use)

## 1. purpose

To evaluate the efficacy, dose-response, and safety of Eppikajutsuto in patients with lymphangitic malformations (LM) in an open-label, pre- and post-administration study. The primary endpoint will be response from baseline in tumor volume by volumetry. Secondary endpoints will be 1. 50% or greater volume reduction, 2. shrinkage rate, 3. 10% improvement in quality of life, 4. safety, and 5. adherence to medications.

---

## 2. background

### 2.1. status of target diseases in Japan and abroad

Lymphatic malformation (LM), a congenital malformation of the lymphatic system, occurs most often in the head and neck region and can cause significant complications such as bronchial compression, especially in children and neonates. LM is a chronic pediatric disease (lymphangioma), and under Japan's universal health insurance system, the main treatment modalities for LM are sclerotherapy and surgical resection. Sclerotherapy is particularly effective for cystic LM, but may be difficult to perform because it causes temporary swelling and compression of vital organs and tissues around the lesion. Surgical resection may also be difficult to implement in diffuse lesions where the lesions are not clearly limited and spread over a large area due to indistinct border growth. Resolution of these problems through less invasive treatment is desired. Recently, the general use of mTOR inhibitors such as sirolimus has been proposed for the treatment of LM in the United States and other countries. In Japan, sirolimus administration for LM is undergoing clinical trials.

The incidence of lymphangitic malformations (lymphangiomas) is unknown, but is estimated to be 1 in 1,000-5,000 births. The exact prevalence is unknown, but the estimated number of patients in Japan is about 10,000. Spontaneous shrinkage is generally considered to be rare, and in two of the eight cases in our retrospective study in which we observed a natural history, the condition of LM was observed to be unchanging or worsening, with no spontaneous remission. The disease did not spontaneously remit in the two cases observed in our retrospective study.

### 2.2. history and content of standard therapies implemented to date

In Japan, the universal health insurance system mainly uses sclerotherapy and surgical resection for the treatment of LM, but less invasive treatments are desired. Recently, sirolimus has been approved in Europe and the United States and proposed as a common agent for LM, but potentially serious side effects have also been reported. Potentially serious side effects of sirolimus have also been reported, including thrombocytopenia, edema, anorexia, anemia, hyperglycemia, hyperlipidemia, hypertriglyceridemia, elevated alkaline phosphatase, elevated serum creatinine, lymphopenia, hypophosphatemia, infection and heart problems. In addition, the cost of continuous dosing of sirolimus is relatively high, at  1,308.8/ mg, and prescriptions of 1 to 4 mg /day are common.

### 2.3. current standard of care and outcomes

As mentioned in 2.2, in Japan, the universal health insurance system provides sclerotherapy and surgical resection for the treatment of LM. According to the Guidelines for the Treatment of Hemangiomas, Vascular Malformations, and Lymphatic Malformations 2017, rated as strength of

recommendation: 2 (weak), across a wide range of treatment sites, treatment methods, age of treatment, and timing of treatment, the case-by-case outcomes for LM are not clear.

#### 2.4. Issues, uncertainties, etc. in the current standard of care that lead to the need for such clinical research

While the standard therapies that have been implemented to date, as described above, are burdensome to patients in terms of side effects and cost, Eppikajutsuto has a high potential to solve these problems.

We were the first in Japan to report the effect of Echisukayaku-zhuyu on lesion reduction in mediastinal LM patients (Figure 1). Subsequently, many institutions have used Echisuyu-Kazhu-to, and in several retrospective case studies, we reported that reduction in mass size was observed in all 2, 8, and 9 cases, respectively. Based on these findings, it was inferred that an increased dose was necessary to achieve a reduction in size. Therefore, in this study, the dose was set at 0.6 g/kg/d in an exploratory manner. Although the insurance coverage for the use of extract is 7.5 g/d, we do not consider this to be particularly problematic, since the dosage is allowed to be increased as needed. The reason for this is that the subject of this study is limited to children, and the dose is doubled at 25 kg when the dose per body weight is doubled, but in this study, the dose is 7.5 g/day at 12.5 kg, so the dose was reduced at 12.5 kg or more. Therefore, the treatment above 12.5 kg can be regarded as treatment at a reduced dose, and it may be possible to evaluate this depending on the number of cases accumulated. There have been no reports of adverse drug reactions at doses such as 0.75 g/kg/d or 7.5 g/d for this dose.

We also reported an infant whose cervical LM was markedly reduced by an increased dose of Koshuizhuyu-tou. Furthermore, we also suggest an mTOR inhibitory effect by Koshui-Kazhu-tan in oral cancer cells.

[figure not shown]

**Figure 1 Changes in mediastinal lymphatic malformations after administration of Chinese herbal medicine**

**a. Before administration b. After 6 months c. After 15 months**

Kesuyu-kazuto costs 11 yen/g, 0.3-0.7 g / kg / day for children, up to 7.5 g / day (= 82.5 yen), and is markedly less expensive than sirolimus.

On the safety front, according to product information from Tsumura Corporation, its side effects

---

include rash, nausea, anorexia, insomnia, palpitations, fatigue, and difficulty urinating, but the rate of side effects is very rare.

Although there are scattered reports on the efficacy of Eppikajutsuto for LM, no evidence has been established to evaluate its efficacy and its dose-dependence and safety.

## **2.5. benefits and disadvantages of protocol treatment**

### **2.5.1. burdens and foreseeable risks to the research subjects**

Participation in this study may result in adverse drug reactions.

### **2.5.2. anticipated benefits to the research subjects**

The lesions may be improved by the effect of Kesuyu Kashuyu on LM.

### **2.5.3. an overall assessment of these and measures to minimize burden and risk**

Evaluate as appropriate for anticipated burdens and risks, and monitor adverse events as appropriate to minimize risk.

## **2.6. Research Design**

This clinical study will objectively establish the efficacy of Eppikajutsuto through an open-label pre- and post-administration comparative study and create evidence for combination therapy with Kampo medicine for LM.

We will prospectively compare the clinical efficacy and safety of Koshuizakazuto in a group of patients treated with LM. The rationale for this study is that Kesui-Saizhu-tou is used for LM patients, and there have been some cases of significant efficacy, so the study will not be conducted using placebo or a non-treated group as a control, but rather a before-and-after comparison between the same patients. In addition, the study will be conducted in a multicenter setting to minimize bias by institution.

## **3. Eligibility Criteria**

### **3.1. selection criteria**

1. patient with LM

(Specific cystic or spongiform lesions, at least on imaging (echo, CT, MRI))

2. weight 25 kg or less

### **3.2 Exclusion Criteria**

A project shall be ineligible if one or more of the following items are met

- 
1. patients with a history of allergic reactions to Koshuyuan
  2. are receiving or have received mTOR inhibitors
  3. who have undergone sclerotherapy or surgery in the past
  4. who have serious diseases other than lymphatic malformations
  5. patients who participated in other clinical studies (trials) within 3 months prior to the start of treatment with the study drug
  6. patients for whom evaluable MRI cannot be performed
- Other patients deemed inappropriate as research subjects by the principal investigator or subinvestigator
- [Rationale] 1)-2)-3)Influence on efficacy evaluation and consideration for safety,  
2)-3)Influence on efficacy evaluation, 4)-7)Consideration for safety

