## **10.3 Analysis Items and Methods**

### **10.3.1. primary endpoint primary analysis method**

For the primary endpoint of the study, the response rate will be based on whether or not patients achieve a reduction in lymphatic malformation volume by volumetry of at least 20% from the pre-treatment level at 6 months of treatment with the drug. An exact method based on a binomial distribution will be used for interval estimation. The significance level for the main analysis is 5% one-sided, and the corresponding two-sided 90% confidence interval is calculated.

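### No eligibility rule covers past or current use of the study drug, so the baseline volume is not guaranteed to be pre-treatment

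*Protocol*

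**What the plan says.** All references are to the protocol.

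- **Inclusion (3.1).** LM shown on imaging, and "weight 25 kg or less". Nothing requires the child to be new to the study drug.
- **Exclusion (3.2).** Children who "are receiving or have received mTOR inhibitors" and those "who have undergone sclerotherapy or surgery in the past" are excluded. The only criterion that names the study drug is "patients with a history of allergic reactions to Koshuyuan". The translation renders the drug's name in several ways; I read this one as Eppikajutsuto. A discretionary item closes the list: "Other patients deemed inappropriate as research subjects by the principal investigator or subinvestigator".
- **Stated reasons (3.2).** "2)-3)Influence on efficacy evaluation, 4)-7)Consideration for safety".
- **Existing use.** Section 2.4 says many institutions have used the drug for LM. Section 2.6 makes that experience a reason for having no control: "there have been some cases of significant efficacy, so the study will not be conducted using placebo or a non-treated group as a control".
- **Baseline scan (0, 5.3 and 6.2).** An MRI that meets the criteria and was taken within 3 months before registration is to be used. No drug-free condition is attached.
- **Primary endpoint (10.3.1).** Response is "a reduction in lymphatic malformation volume by volumetry of at least 20% from the pre-treatment level at 6 months of treatment with the drug".

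**The concern.** The trial has one arm, and its efficacy conclusion rests on comparing each child with the same child before the drug. That works only if the baseline scan precedes exposure. The protocol applies this reasoning to other active treatments but not to the treatment under test.

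Three routes lead to a wrong baseline or a selected sample:

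- **Drug taken before the baseline scan.** Some shrinkage may already be in the baseline, which lowers the observed response.
- **Drug started between the baseline scan and Day 0.** That exposure is credited to the 6-month course, which raises the observed response.
- **Past user known to have responded whose lesion regrew after stopping.** Enrolling such a child would also raise the response.

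The safety endpoint and the adherence endpoint (the share taking at least 70% of their medication, 9.2) would tend to look better if exposed children who tolerated the drug were included.

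**Working it through.** **1. Does any eligibility rule stop an exposed child?** Take a child with LM, under 25 kg, given Eppikajutsuto off-label, without allergy, and with no mTOR inhibitor, sclerotherapy or surgery.

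- Both criteria in 3.1 are met.
- Criteria 1 to 3 of 3.2 do not apply. Criteria 4 to 6 concern other serious disease, participation in other studies and MRI feasibility. Routine prescribing is not study participation.
- Only the discretionary item remains. It appears to be item 7 in the rationale line, where items 4 to 7 are justified by safety, not by efficacy evaluation.
- Sections 5.3 and 5.4 state no washout. The prohibited treatments in 5.4 are sclerotherapy, resection and mTOR inhibitors.

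**2. Does any later step catch the child?**

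- The registration centre (4.1) verifies eligibility, and there is no written criterion on this point to verify.
- Previous treatment is recorded before the start (6.1), but no rule uses it.
- The full analysis set drops violations of important exclusion criteria, and the per-protocol set requires no serious eligibility violation (10.2). This child violates none, so prior exposure removes the child from neither set.

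**3. Timeline.** The baseline scan may be up to 3 months before registration, and dosing starts right after enrolment (5.3.4). Use that began just after the scan could add up to about 3 months of exposure to the planned 6.

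**4. The protocol's own figure (10.1).** The exact two-sided 90% interval for 9 of 18 is:

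- lower limit = 5% quantile of Beta(9, 10) = 29.12%
- upper limit = 95% quantile of Beta(10, 9) = 70.88%

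The protocol gives 29.1% and 70.8%, so the figure reproduces; the upper limit was truncated. It does not depend on this point.

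**5. Illustration.** Let m of the 18 analysed children be exposed, with response rate p1, and let the rest respond at p0. The expected rate is ((18 − m)·p0 + m·p1)/18. The 50% and 83% are the planning and retrospective rates in 10.1. The values of m, the 10% and the 30% are assumptions, and so is applying 83% to exposed children.

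| p0 | m | p1 | Calculation | Expected rate |
|---|---|---|---|---|
| 50% | 4 | 83% | (14×0.50 + 4×0.83)/18 = 10.32/18 | 57% |
| 50% | 4 | 10% | (14×0.50 + 4×0.10)/18 = 7.40/18 | 41% |
| 50% | 6 | 83% | (12×0.50 + 6×0.83)/18 = 10.98/18 | 61% |
| 50% | 6 | 10% | (12×0.50 + 6×0.10)/18 = 6.60/18 | 37% |
| 30% | 6 | 83% | (12×0.30 + 6×0.83)/18 = 8.58/18 | 48% |

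One child in 18 is worth 1/18 = 5.6 points. In the last row a true 30% in unexposed children would look close to the planned 50%.

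**The case against.** **Intent.** The protocol reads as if children start untreated. The drug is taken after consent (5.3.2), treatment begins only after registration is confirmed (4.1), and outcomes are measured from before the start of the drug (10.3.3). A child already taking it has no pre-treatment level in any ordinary sense, and an investigator could use the discretionary exclusion. This stands as evidence of intent, but none of it is a rule, and it says least about past users and about use that starts between the scan and Day 0.

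**Size.** The protocol gives neither the number of exposed children nor how they would respond. The 83% is a retrospective response to treatment, not the response to a further course, and section 10.1 itself discounts it to 50% for overestimation. All the illustrated shifts from 50% stay within the planned 90% interval, and the trial is exploratory, with no threshold response rate stated. This stands in full: the table shows sensitivity and is not an estimate.

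**Stronger readings.** A reader might infer that the response rate will be inflated by known responders, or that the bias differs by site according to local prescribing. The documents support neither. The direction is undetermined, there are no prescribing data for the seven sites, and nothing shows that an exposed child was enrolled.

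**Breadth of the remedy.** A lifetime ban would also remove a child once given the drug for a labelled use such as eczema (5.1), with no shown effect on the baseline. This stands, and it narrows the fix.

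**Conclusion.** The gap is real and more than a missing detail. Criteria 2 and 3 exclude other active treatments because they influence the efficacy evaluation. The same reason applies to the study drug, yet exposure to it is not addressed at eligibility, at the baseline scan or in the analysis sets. In a before-and-after design without a control, the reference value of the primary endpoint can therefore be wrong for any exposed child.

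The direction and size of the bias are unknown. With 18 analysed children a handful of exposed ones could move the rate by several points either way; with 4 of 18, the illustration runs from 41% to 57% around 50%. This rests on assumed numbers and response rates. The planned sample size and its interval are unaffected. The point should be fixed, but it does not invalidate the design.

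**What to change.** 1. Add to 3.2, and to the registration eligibility form, an exclusion for children who are currently receiving Eppikajutsuto or who received any between the baseline MRI and Day 0. State that the baseline MRI must be drug-free up to Day 0.
2. For earlier use, choose one rule and write it down. Either exclude prior use for LM, on the rationale already given for criteria 2 and 3, or keep these children and report the response rate with and without them, using the previous-treatment data collected under 6.1.

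**Cost.** A line or two in 3.2 and on the form. The target of 20 and the 9-of-18 interval do not change. The pool becomes slightly smaller, which matters because 10.1.1 calls 20 cases close to the limit of feasibility. The figures in 10.1 and 7.1 (about 5 patients per site per year × 7 sites × 3 years = 105 seen) should not be read as ample room, because they count patients seen, and no allowance for the weight limit or the existing exclusions is shown. Limiting the rule on earlier use to LM keeps the loss small.

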## **4. registration and allocation**

### **4.1. case registration procedure**

- 1) The principal investigator or subinvestigator obtains written consent from the research subject and the surrogate.
- 2) After obtaining consent, the principal investigator or subinvestigator will enter the necessary information (date consent was obtained, subject identification code, subject name, medical record number, etc.) that corresponds to the research subject and subject identification code in the list of research subjects kept by the principal investigator (or personal information manager, if a personal information manager is separately appointed). ), and the principal investigator (or personal information manager) will keep the list of research subject identification codes (or list of research subjects or register of research subjects) in a lockable place under his/her control.
- 3) After confirming that all selection criteria are met and none of the exclusion criteria are violated, the principal investigator or subinvestigator should complete the case registration form with the necessary information, including the subject identification code, and fax it to the case registration center.
- 4) The case registration center will verify eligibility and, if there are no eligibility issues, will prepare a registration confirmation form with the subject registration number and fax it to the principal investigator or research assistant.
- 5) After receiving and reviewing the registration confirmation form, the principal investigator or subinvestigator will initiate the protocol treatment.
- 6) In the event of withdrawal of consent, discontinuation, dropout, etc., the Principal Investigator shall be promptly informed.

### **4.2 Allocation Method and Allocation Adjustment Factors**

No allocation

## 5. clinical research plan

### 5.1. Summary of Test Drugs

Test drug: Koshui-Kazuzu-to (product name: Tsumura Koshui-Kazuzu-to®, product number: 028)

Manufacturer (or distributor): Tsumura Corporation

Classification: Kampo formula

Indications: nephritis, nephrosis, beriberi, rheumatoid arthritis, nocturia, eczema

Route of administration, dosage, and directions for use (as indicated on the package insert):

The usual adult dosage is 7.5 g orally per day in two to three divided doses before or between meals. The dosage may be adjusted according to age, weight, and symptoms.

Contraindications: None

Main clinical use results: Action on dermatitis

Pre-mixing administration to mice suppressed primary irritant contact dermatitis caused by croton oil and allergic contact dermatitis caused by DNFB.

Side effects/defects:

- Serious side effects

Pseudohypoaldosteronism: Pseudohypoaldosteronism such as hypokalemia, elevated blood pressure, sodium and fluid retention, edema, and weight gain may occur.

Myopathy: Since myopathy may occur as a result of hypokalemia, patients should be carefully monitored. If abnormalities such as weakness, limb cramps or paralysis are observed, administration should be discontinued and appropriate measures such as administration of potassium agents should be taken.

Other side effects (frequency unknown)

Hypersensitivity: rash, redness, itching, etc.

Autonomic nervous system: insomnia, excessive sweating, tachycardia, palpitations, general weakness, mental agitation, etc.

Gastrointestinal: anorexia, gastric discomfort, nausea, vomiting, soft stool, diarrhea, etc.

Urinary organs: dysuria, etc.

Interactions: [Concomitant use precautionary statement].

The following drugs should be carefully administered: mallow-containing preparations, ephedrine-containing preparations, monoamine oxidase (MAO) inhibitors, thyroid preparations, thyroxine, liothyronine, catecholamine preparations, adrenaline, isoprenaline, xanthine preparations, theophylline, diprophyrin (since insomnia, excessive sweating, tachycardia, palpitations, general weakness, mental agitation, etc. are more likely to occur, the dosage should

---

be reduced or otherwise carefully administered), and other drugs. The dosage should be reduced or otherwise administered with caution since insomnia, excessive sweating, tachycardia, palpitations, general weakness, and mental agitation are more likely to occur.)

Preparations containing cambogia, glycyrrhizic acid and its salts (Pseudohyperaldosteronism is more likely to occur. Also, myopathy is more likely to occur as a result of hypokalemia.)

#### Usage Notes:

careful administration

1. Patients in the post-illness debilitated phase or those with significantly diminished physical strength [adverse reactions may be more likely to occur and symptoms may be intensified].

2. Patients with a weak gastrointestinal tract [Anorexia, gastric discomfort, nausea, vomiting, soft stools, diarrhea, etc. may occur.]

3. Patients with anorexia, nausea, and vomiting [these symptoms may worsen].

4. Patients with a marked tendency to perspire [excessive sweating, general weakness, etc. may occur.]

5. Patients with angina pectoris, myocardial infarction, or other circulatory disorders, or with a history of such disorders

6. Patients with severe hypertension

7. Patients with severe renal impairment

8. Patients with dysuria

9. Patients with hyperthyroidism [5-9: These diseases and symptoms may worsen.]

important basic precautions

When using this product, the patient's signs (constitution and symptoms) should be taken into consideration. The course of the patient should be carefully monitored, and if there is no improvement in symptoms and findings, continued administration should be avoided.

Since this drug contains cimpanzamide, serum potassium and blood pressure levels should be carefully monitored, and administration should be discontinued if any abnormality is observed.

When other Kampo formulas, etc. are used concomitantly, care should be taken not to duplicate the herbal ingredients contained in the product.

See Appendix in "25. Appendix."

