## 6.2. schedule for observation, inspection and reporting

### Observation, Inspection and Reporting Schedule

| (data) item                          |                 | Consent and screening                          | protocol treatment        | outcome study | time of discontinuance     |
|--------------------------------------|-----------------|------------------------------------------------|---------------------------|---------------|----------------------------|
| time                                 |                 | before the start of the test                   | Day 0 Day28 Day 84 Day168 | Day365        | Date of Decision to Cancel |
| Obtaining Consent                    |                 | ○                                              |                           |               |                            |
| Confirmation of medication adherence |                 |                                                | ○ ○ ○                     |               |                            |
| Background check                     |                 | ○                                              |                           |               |                            |
| test drug administration             |                 |                                                | ←→                        |               |                            |
| Observation of adverse events        |                 | ○                                              | ←→                        |               |                            |
| clinical examination                 | hematology      |                                                | ○ ○ ○ ○                   | △             | ○
○                     |
|                                      | blood chemistry |                                                | ○ ○ ○ ○                   |               |                            |
| MRI                                  |                 | ○note
(supplementary information)
symbol | ○                         | △             | ○                          |
| EO-5D-5L                             |                 |                                                | ○ ○                       |               |                            |

△Implementation: Implemented when possible

\*If there are MRI images that meet the criteria within 3 months prior to registration, they should be used.

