## **8.2. evaluation and reporting of adverse events**

In this clinical study, adverse events and side effects will be evaluated using CTCAE v4.0-JCOG, with adverse events listed and graded. Grading of adverse events will be based on the closest definition of Grade 1 to 4, respectively. If a specific treatment is listed in the Grade, it should be graded based on its clinical necessity. In this study, an adverse event is judged as a Grade worsening by one or more levels in CTCAEv4.0. Abnormal laboratory values are also graded in the same way. Adverse events that occurred prior to treatment with the study drug will also be reported as adverse events if the Grade worsens by one or more levels.

Severity of adverse events

The severity of the adverse event shall be one of the following

1. non-serious

2. serious

Causality Classification

The causal relationship to the study drug and protocol treatment will be determined by one of the following categories, respectively

1. causality cannot be ruled out: there is a reasonable causal relationship with the study drug or protocol treatment (including cases where causality is unknown due to insufficient information)

2. causality can be ruled out: there is no reasonable causal relationship to the study drug or protocol treatment.

Adverse Event Outcomes

Adverse event outcomes shall be classified as one of the following categories.

1. recovery: adverse event returned to Grade 0 in CTCAE v4.0 or Grade prior to study drug administration

- 
2. minor: adverse event returned to Grade 1 in CTCAE v4.0 (applies to AEs Grade 2 or higher)
  3. unrecovered: Adverse event has not resolved and is in the same Grade as when the adverse event occurred.
  4. recovered but with sequelae: adverse events resolved but with sequelae
  5. death: The research subject has died
  6. unknown: no information, unknown outcome

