### **8.3. anticipated adverse events**

Serious Side Effects of Kesuyu Kashuyu

- 1) Pseudohyperaldosteronism: frequency unknown
- 2) Myopathy: frequency unknown

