## 9.2. secondary endpoints

1. percentage decrease of more than 50% of volume

2. lesion reduction rate

3. 10% improvement in quality of life associated with treatment

4. safety of administration of koshuizhuyuu

5. adherence to the administration of Koshuizhuyuu (percentage of patients who were able to take

---

at least 70% of their medications)

Rationale: 3) Even if there is no marked change in size, QOL and symptom improvement has been reported, so it was set as a secondary endpoint; 4) Pseudohyperaldosteronism is known to be a major side effect of Eppikajutsuto, but its occurrence in children is not well reported.

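### Section 5.1 makes raised blood pressure a reason to stop the drug, but Sections 6.1 and 6.2 schedule no blood-pressure reading, not even at baseline

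*Protocol*

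**What the plan says.** Section 5.1 describes the drug's serious side effect as one in which "hypokalemia, elevated blood pressure, sodium and fluid retention, edema, and weight gain may occur". Its usage notes ask for caution in "Patients with severe hypertension" and add that "serum potassium and blood pressure levels should be carefully monitored, and administration should be discontinued if any abnormality is observed".

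Section 8.3 lists the same risk among the anticipated serious effects: "Pseudohyperaldosteronism: frequency unknown". Section 9.2 gives it as the reason for the safety endpoint: "Pseudohyperaldosteronism is known to be a major side effect of Eppikajutsuto, but its occurrence in children is not well reported".

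Section 6.1 sets out what is measured and when. Biochemistry, including sodium and potassium, is due before the start and on Days 28, 84 and 168. Height and weight are among the baseline items. Blood pressure and vital signs are not listed at any visit. The table in 6.2, headed "Observation, Inspection and Reporting Schedule", has rows for consent, adherence, background, drug administration, adverse events, hematology, blood chemistry, MRI and EQ-5D-5L, and none for blood pressure.

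Section 8.2 states that "an adverse event is judged as a Grade worsening by one or more levels in CTCAEv4.0", and one of its outcome categories is "recovery: adverse event returned to Grade 0 in CTCAE v4.0 or Grade prior to study drug administration".

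**The concern.** The precaution in 5.1 names two measurements and attaches one action to both. The schedule supplies the first and leaves out the second, so a site can follow 6.1 and 6.2 to the letter and never obtain the reading that would prompt stopping.

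Two things are at stake. The first is safety. A child whose blood pressure rises while potassium stays normal may remain on treatment. Treatment lasts 6 months at 0.6 g/kg/day, capped at 7.5 g/day. A child of 12.5 kg reaches that cap (0.6 × 12.5 = 7.5 g), and 5.1 gives 7.5 g as the usual adult daily dose. Section 3.1 admits children up to 25 kg, so any participant from 12.5 kg upward takes the full adult amount.

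The second is the safety endpoint. Section 10.3.3 plans to report the type and frequency of adverse events. For this sign the frequency would depend on local habit at seven sites, although the protocol says that the effect is poorly described in children.

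**Working it through.** The plan states no figure to reproduce. The check sets the precaution in 5.1 against the item list and the schedule, then counts.

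**Step 1: coverage of the 5.1 precaution**

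| Time point | Potassium (6.1) | Blood pressure (6.1 and 6.2) |
|---|---|---|
| Before the start | yes | not listed |
| Day 28 | yes | not listed |
| Day 84 | yes | not listed |
| Day 168 | yes | not listed |
| Discontinuation (6.2 column) | blood tests marked | not listed |

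In the available text, blood pressure appears only in the side-effect description and the precaution in 5.1.

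**Step 2: planned values.** With 20 patients (7.1) and 4 chemistry time points (6.1):
- potassium in total: 20 × 4 = 80
- potassium on treatment: 20 × 3 = 60
- blood pressure: 0

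**Step 3: can 8.2 be applied?** An adverse event needs a worsening of at least one grade, so it needs a starting grade. Recovery may mean a return to the pre-treatment grade, which needs the same value. Potassium has both a baseline and repeat readings. Blood pressure has neither by plan, so its grading would rest on whatever a site recorded in routine care.

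**Step 4: weight of one site.** The targets in 7.1 are 3, 4, 3, 3, 3, 2 and 2, which sum to 20. A site that does not measure routinely would remove between 2/20 = 10% and 4/20 = 20% of patients from ascertainment of this sign. The protocol does not show how many sites, if any, would fail to measure.

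**Step 5: illustration only; both inputs are assumed.** Let *p* be the proportion of children with a rise in blood pressure but no hypokalemia, and *c* the share of those caught by unscheduled readings. Then expected missed cases = 20*p*(1 − *c*), and the chance of recording no case = (1 − *pc*)^20.

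| *p* | Expected cases (20*p*) | Missed, *c* = 0.75 to 0.25 | P(none recorded), *c* = 1 | *c* = 0.75 | *c* = 0.25 |
|---|---|---|---|---|---|
| 0.05 | 1 | 0.25 to 0.75 | 0.358 | 0.466 | 0.778 |
| 0.10 | 2 | 0.5 to 1.5 | 0.122 | 0.210 | 0.603 |

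For example, at *p* = 0.10 and *c* = 0.25: 1 − 0.025 = 0.975, and 0.975^20 = 0.603.

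**The case against.** The strongest reply is that the sentence in 5.1 is product information. It stands among general precautions, next to text taken from the package insert, while the trial's own discontinuation rules are in 5.6, which names neither potassium nor blood pressure. On this reading no trial rule is contradicted. That is fair as to status: it is a precaution, not a formal stopping criterion. But the protocol includes it in its clinical research plan and nothing overrides it, and the other measurement it names is scheduled.

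Other safeguards also exist:
- Investigators are still told to monitor.
- Adverse events are observed from the start of treatment until 4 weeks after it ends, and any unfavourable sign counts.
- Section 5.6 allows stopping for adverse events and calls for necessary tests at discontinuation.
- Scheduled potassium catches the cases with hypokalemia.
- Exclusion 4 and investigator judgement should keep out most children with serious hypertension.

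These points narrow the gap to fixed timing and a recorded baseline; monitoring is not wholly absent. They do not close it. Raised blood pressure is generally not recorded unless someone measures it, tests made once stopping is decided cannot prompt that decision, and potassium does not show a rise that occurs without hypokalemia.

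It can also be said that other listed effects, such as palpitations and sweating, have no scheduled item. Those can be noticed and reported by the child or family, and 5.1 does not single them out for monitoring.

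Finally, the numerical illustration has no basis in the protocol, and at a true 5% even full capture would record no case in 20 children 36% of the time. That stands. The conclusion does not use the illustration.

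**Conclusion.** The point holds. The protocol schedules potassium at four time points and blood pressure at none, although 5.1 asks for both and tells investigators to stop the drug if either is abnormal. The size that follows from the document is 80 planned values against 0. The number of cases missed cannot be derived.

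The primary endpoint and the sample size are untouched. The effect falls on patient safety and on the completeness of a descriptive safety listing in an exploratory study of 20 children. It should be fixed, because the sign belongs to the very effect that justifies the safety endpoint and the remedy is cheap.

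The conclusion rests on 6.1 and on the legible rows of 6.2, which agree. The flow figures, the appendix and the case report form were not available. If any of them requires blood pressure at set visits, the remaining task is to bring 6.1 and 6.2 into line. That a child would actually stay on treatment with raised blood pressure is a possibility, not something the document shows.

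**What to change.** Add blood pressure to 6.1, to the 6.2 schedule and to the case report form: before treatment, on Days 28, 84 and 168, and at discontinuation. State an age-appropriate threshold for stopping, so that the precaution in 5.1 can be applied in the same way at every site. Grade readings under 8.2 against the baseline value, and tabulate them beside potassium in the safety analysis.

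The cost is one row in the schedule and the form, a few minutes at visits that already include a blood draw, and a protocol revision under 15.2. No new visit or invasive procedure is needed.

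Optionally, record body weight at the same visits to document the dose per kilogram, read against expected growth. This is minor.
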